The project involves four work packages. Three of these are prospective empirical studies amongst people living with BD. Study 1 (WP1, Australia) aims to predict early relapse by modelling RAR data. Study 2 (WP2, India) tests predictive models from RAR developed in Study 1 and tests the mechanistic relationship between a key RAR variable (Relative Amplitude, representing circadian robustness) and diurnal amplitude of gene expression and metabolites in blood. Study 3 (WP3, New Zealand) advances mechanistic understanding of the link between RARs and mood in BD by investigating a different state transition, namely, recovery from an acute episode, operationalised in response to evidence-based treatment. Thus, Studies 1 and 2 contribute to the project’s primary aim of algorithm development, and Studies 2 and 3 contribute (in different ways) to the secondary aim of improved mechanistic understanding of RAR variables in predicting BD course. Finally, WP4 is computational, conducting model comparison, cross-validation and synthesis using ensemble machine learning. A key output of WP4 is an open dataset and computational pipelines for sharing with future researchers.

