### Inclusion and exclusion criteria

2.1

The approach to sampling and inclusion/exclusion balances four principles: maximising generalisability of findings, maximising inclusivity for people living with BD, participant empowerment and duty of care.

*All studies*

In all studies, participants must have a diagnosis of BD I or II confirmed by structured clinical interview. Reason to believe that participation would interfere with treatment and/or recovery is an exclusion criterion. Participants must have sufficient language fluency (English in Studies 1 and 3; English, Hindi, Telegu, or Bengali in Study 2) to be able to provide informed consent and to complete self-report and interview-based assessments. Age range for inclusion is 18–65 years. This range was selected to limit variance associated with the distinct circadian and sleep changes of adolescence and later life and is conventional for operationalising the ‘adult’ life phase in mental health research. Similarly, age 65 is a common cut-off in BD [e.g.,
70] and sleep/circadian research [e.g.,
40].

Presence of a physical problem that might confound RAR interpretation is an exclusion. The decision about whether to exclude is made case-by-case, considering the sampling principles of generalisability and inclusivity (above). Screening for this exclusion differs by study. In Studies 1 and 2, participants are asked at screening about any physical conditions that impact movement, which are then followed up at interview. In Study 3, nurses involved in recruitment are trained to observe for movement (particularly Parkinsonian tremor in the inpatient setting) as a potential exclusion.

Presence of common BD comorbidities is not an exclusion criterion. Anxiety disorders, substance use disorders and sleep disorders will be assessed by structured clinical interview at baseline and explored for potential inclusion in predictive models. This approach allows us to build models that generalise to complex clinical presentations while still accounting for their impact on models.

*Study 1 and 2*

In Study 1 and 2, being in an episode
*at baseline* is an exclusion criterion. Following common cut-offs [e.g.,
71,
72] presence of an episode is defined as a score of > 12 on the Montgomery-Asberg Depression Rating Scale [MADRS,
73], or > 8 on the Young Mania Rating Scale [YMRS,
74] [

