**Figure 2. f2:**
[figure not shown]
Study 2 design overview.

Three research questions and two hypotheses are therefore set for Study 2:
•Research Question 1: Does the Cox Survival Analysis model derived in Study 1 replicate amongst
*N* = 25 BD participants in an LMIC cohort?•Research Question 2: Does Dynamic Bayesian Network Analysis enable examination of relapse prediction amongst
*N* = 25 BD participants in an LMIC cohort?•Research Question 3: Does Hadaeghi’s Complex System Model of relapse prediction derived in Study 1 replicate amongst
*N* = 25 BD participants in an LMIC cohort?•Hypothesis 1: Amongst the complete sample (
*N* = 50), Relative Amplitude will correlate with the diurnal amplitude of both circadian gene expression and blood metabolites.•Hypothesis 2: Diurnal amplitude of circadian gene expression and blood metabolites, and Relative Amplitude will be attenuated in people with interepisode BD (
*N* = 25) compared to age, gender, and employment-matched healthy controls (
*N* = 25).

*Study 3: Exploring generalisability of the Complex System model of state transition from relapse prediction to treatment response.*

Study 3 contributes to the project’s secondary mechanistic aim by investigating if complex system features found in Study 1 to predict relapse (state transition into an episode) generalise to prediction of treatment response from an acute episode (state transition to recovery). If generalisation is demonstrated, it could be hypothesised that Hadaeghi’s Complex System Model captures generic system instability (as opposed to a relapse-specific process).

The primary aim of Study 3 is therefore to investigate whether the relapse risk algorithm informed by Hadaeghi’s Complex System Model (trained and tested on Study 1 data) can be extended to response to treatment.
^
19
^ The state transition of Study 3 is measured in binary response to treatment. Response to treatment at 8 weeks is operationalised as 50% reduction in MADRS (for those in depressive episode at baseline) or 50% reduction in YMRS (for those in manic episode at baseline). Participants will wear actigraphs for 21 days – for consistency with Study 1 and 2, the first 14 days only will be used in modelling of binary response to treatment.
Figure 3 below summarises the study design for this primary aim.

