Survival analysis has shown that the probability of recovery is significantly lower from major depressive episodes compared to mania or hypomania. Recovery is also less likely from cycling episodes (switching between poles without a recovery period). This means that, ideally, manic and depressive episodes should be analysed together (suggesting a joint survival model for these two types of episode), but it is unclear if we will have sufficient data for this. Decisions will be made on review of the complete dataset and reported in the statistical analysis plan (forthcoming).

*Dynamic Bayesian Network Analysis*

Network analysis is a variant of machine learning designed to illuminate the architecture of complex systems.
^
97
^ In this project, network analysis is used to model potential causal pathways amongst sleep and circadian variables in the prediction of relapse. The analysis generates a graphical representation of nodes (individual characteristics and variables) and edges (connections and links among nodes). Location of nodes and strength/valence of links between nodes represent the specific association between two nodes while controlling for all other variables.

Scott and colleagues recently undertook a pilot study in a sample of young people with emerging BD and produced a network model of RAR variables relative to each other and to phenotypic features of BD.
^
33
^ This study found further support for the importance of robust circadian rhythmicity as measured in Relative Amplitude (see above). However, the authors highlight significant uncertainties in their modelling outcomes, concluding that “… whilst all research findings require replication and confirmation, we stress that this is particularly important in this emerging field of research” (p. 225).

The network analysis of Scott et al. was developed using cross-sectional data, while the present prospective project will permit exploration of how RAR variables change in relation to each other and to other BD symptoms over time. To model these temporal dependencies, Dynamic Bayesian Network Analysis will be applied. Dynamic Bayesian Networks are well suited to representing probabilistic relationships that evolve dynamically and can therefore capture time-dependent causal pathways among RAR, sleep, and clinical variables [see, e.g.,
100,

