The primary input data for all predictive modelling in Studies 1, 2 and 3 will consist of 14 days actigraphy time-series and derived features extracted through both time-domain and frequency-domain analyses. Feature extraction will include conventional RAR metrics such as the Van Someren variables (Relative Amplitude, Intradaily Variability, and Interdaily Stability), sleep–wake regularity, rhythm phase, and fragmentation, as well as signal-based features obtained from Fourier and wavelet analyses that capture periodicity, spectral power distribution, and nonstationary temporal patterns. Together, these actigraphy-derived metrics will form the principal set of predictors for analyses based on Cox Survival Analysis, Dynamic Bayesian Networks, Hadaeghi’s Complex System Model of BD and other machine learning approaches to be explored.

Auxiliary variables, including demographic and clinical data, will be used to support feature interpretation and to define model outcomes. In Studies 1 and 2, the primary outcome will be relapse, defined as the onset of a new depressive, manic or hypomanic episode meeting DSM-5 diagnostic criteria. Relapse will be identified through structured follow-up interviews using the LIFE (above). Time to first relapse will also be analysed as a survival outcome. In Study 3, the primary outcome will be treatment response, defined as at least a 50% reduction in baseline MADRS or YMRS scores at 8-week endpoint.

These outcome variables will be used to label actigraphy epochs and to train, validate, and compare predictive models of relapse risk and treatment response.

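### Study 3's recovery label reads only the baseline-pole scale, so a participant who has switched pole by week 8 is scored as recovered

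*Protocol article*

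**What the plan says.** Section 2.2 of the protocol article (Study 3) states that "The state transition of Study 3 is measured in binary response to treatment". The rule follows: "Response to treatment at 8 weeks is operationalised as 50% reduction in MADRS (for those in depressive episode at baseline", and for the other pole "or 50% reduction in YMRS (for those in manic episode at baseline". Box 1, the secondary aim of Study 3 in section 2.2, section 2.4 and section 2.6 repeat the 50% threshold. Section 2.6 has it "defined as at least a 50% reduction in baseline MADRS or YMRS scores at 8-week endpoint". None of these places adds an end score to be reached or a condition on the other scale. Sections 2.4 and 2.6 do not tie the scale to the baseline pole; section 2.2 does.

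The article also says what this outcome stands for. Section 1.4 describes the third study's transition as "recovery from an acute episode, operationalised in response to evidence-based treatment". Section 2.2 asks whether the features that predict relapse "generalise to prediction of treatment response from an acute episode (state transition to recovery". Box 1 adds recovery in brackets after treatment response.

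Three statements elsewhere bear on this:

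- Section 2.1, for Studies 1 and 2: "presence of an episode is defined as a score of > 12 on the Montgomery-Asberg Depression Rating Scale", or above 8 on the YMRS.
- Section 2.4: relapse in Studies 1 and 2 is any manic, hypomanic or depressive episode, assessed with the LIFE interview.
- Section 2.6 (Cox Survival Analysis): "Recovery is also less likely from cycling episodes (switching between poles without a recovery period".

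**The concern.** Study 3 asks whether a model of moving into an episode also forecasts moving out of one. Its label does not establish that the participant has left an episode, for two reasons.

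First, the rule looks at one pole. A manic participant who is depressed at week 8 will usually have a low YMRS and be counted as a responder. A depressed participant who has become manic can be counted in the same way. The article's own account of switching is that no recovery intervenes, and section 2.6 presents switching as a central nonlinear feature of the illness.

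Second, halving a score measures improvement. Where the participant ends up depends on where they started, and Study 3 enrols severe episodes (CGI of 5 or more).

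At stake is what Research Questions 1 and 2 of Study 3 can conclude. They combine Study 1 relapse labels with Study 3 response labels in one model, and section 2.2 would read successful generalisation as a sign of generic system instability. If the positive class mixes recoveries with switches, a good or poor fit cannot be attributed to recovery alone.

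**Working it through.** The article gives no sample-size or power figure for Study 3 that could be reproduced, so the check is of the definition itself.

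**Inputs**

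- Response: at least a 50% fall on the baseline-pole scale at week 8 (section 2.2, Box 1, section 2.6).
- Episode cut-offs in Studies 1 and 2: MADRS > 12 or YMRS > 8 (section 2.1, and again under risk management in section 2.7).
- Study 3 entry: CGI of 5 or more, with no MADRS or YMRS minimum (sections 2.1 and 2.3).
- Study 3 size: 30 depressed + 15 manic = 45 (sections 2.2 and 2.6).

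**Step 1: opposite pole.** Take a depressed participant who goes from MADRS 30 to MADRS 10 and has YMRS 20 at week 8 (hypothetical scores).

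- Fall on MADRS: (30 − 10)/30 = 66.7%, which is at least 50%, so the participant is a responder.
- YMRS 20 > 8, so the participant meets the project's episode criterion at the other pole.

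The rule never reads the YMRS for this participant, so the result does not depend on the baseline score. The mirror case holds for a manic participant.

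**Step 2: same pole.** Scores are integers. From baseline b, the highest week-8 score that still counts as response is floor(b/2). A responder can remain above a cut-off c when floor(b/2) > c.

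- MADRS, c = 12: floor(b/2) ≥ 13, so b ≥ 26 (26 to 13 is exactly 50%). From b = 25 the highest responding score is 12, which is not above the cut-off.
- YMRS, c = 8: floor(b/2) ≥ 9, so b ≥ 18 (18 to 9 is exactly 50%). From b = 17 the highest responding score is 8.

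The fall needed to reach the cut-off is (b − c)/b:

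| Baseline | MADRS, to reach 12 | YMRS, to reach 8 |
|---|---|---|
| 18 | 33.3% | 55.6% |
| 26 | 53.8% | 69.2% |
| 30 | 60.0% | 73.3% |
| 40 | 70.0% | 80.0% |

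Below MADRS 26 or YMRS 18, every responder is at or under the cut-off on the index scale. At or above those values, a responder may or may not be.

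**Step 3: number affected.** This would need the baseline score distribution, the distribution of week-8 change and the switch rate. The article gives none of them, so no count or percentage of the 45 can be derived.

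**The case against.** The outcome is consistently named treatment response, and a fall of at least 50% is a coherent definition of response. On that view the defect is loose wording. This stands as far as the response outcome goes, and there is no reason to discard it. It does not settle the matter, because section 2.2 makes the same variable the measure of the state transition, and section 1.4 and Box 1 equate it with recovery.

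A reader might infer that a label requiring both scores to be at or under the cut-offs would give Study 3 the same boundary as Study 1. The documents do not support that. MADRS > 12 and YMRS > 8 serve as the entry exclusion and the follow-up review trigger in Studies 1 and 2. Relapse is labelled from the LIFE interview against DSM criteria (sections 2.4 and 2.6). A week-8 MADRS of 13 to 15 is above a screening cut-off; it is not shown to be a DSM episode.

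A reader might also infer that a large share of responders would still be in an episode, or that the mislabelling is worse in mania and so distorts Research Question 3. From equal baselines the YMRS does need the larger fall, but whether the groups differ in mislabelling depends on baselines and changes that the article does not give.

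It can further be said that a switch is itself a critical transition, so coding it as no change would be wrong too. That is fair, and it argues for a category of its own.

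Finally, the project calls itself exploratory, Study 3 serves a secondary aim, and detailed assessment schedules are left to study-level protocols. These points limit the severity. They do not remove a rule that is already fixed in this article.

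**Conclusion.** The point holds in a limited form. As written, the rule labels a participant who has switched pole by week 8 as having made the transition to recovery, whatever the baseline score, provided that the index scale has halved. This follows from the text alone. It conflicts with counting an episode at either pole as relapse and with the article's description of switching.

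The second part is conditional. A responder can still be above the entry cut-offs of Studies 1 and 2 only from a baseline MADRS of 26 or YMRS of 18 upward. Such baselines are plausible in severe episodes, but that is an assumption.

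The number affected among the 45 is unknown. A reader might conclude that Study 3's answer is uninterpretable; the documents do not support that, because without a switch rate the effect could be small. This is an inexpensive improvement that sharpens what Research Questions 1 and 2 can say about recovery, and it is no fatal flaw.

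**What to change.** 1. Reconcile response with recovery in section 1.4, Box 1 and section 2.2, so that the 50% rule is not presented as recovery without qualification.
2. Keep the 50% reduction on the index scale as the primary response outcome.
3. State that MADRS and YMRS are both recorded at week 8 for every participant, whatever the baseline pole.
4. Do not label as recovery anyone who meets the project's existing episode cut-off on the opposite-pole scale at week 8. Report these participants as a separate switch category, and state before analysis how the binary models treat them.
5. Repeat Research Questions 1 to 3 as a sensitivity analysis in which the positive label is a week-8 score not above either existing cut-off (MADRS ≤ 12 and YMRS ≤ 8). Describe it as a stricter outcome, without claiming that it matches the LIFE-based relapse label.

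Cost: edits to wording and, if not already planned, one short scale at week 8. Both scales are already listed for weekly rating over the 21 days (sections 2.2 and 2.4), so the raters know them. The sensitivity label will give fewer positives in a sample of 45, so its estimates will be less precise. Timing matters: section 2.9 says that data collection has begun, and an opposite-pole score not taken at week 8 cannot be recovered later.

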## Protocol

2.

To ensure clarity and appropriate detail for a project with this hierarchical structure, a multi-paper registration strategy has been adopted. Study-specific methodological details essential for direct replication of each component (e.g., detailed assessment schedules, site-specific recruitment procedures, and embedded sub-studies) will be provided in three forthcoming, cross-referenced study-level protocols [
2]. This manuscript presents the overarching project protocol, detailing the scientific rationale, the high-level design of the three empirical studies, and the cross-study analytic plan (WP4).
Box 1 provides an overview and comparison of the three studies’ methods.

Box 1. Comparison of methods across three empirical work packages.**Table T1:** 

Design Feature	Study 1 (Australia)	Study 2 (India)	Study 3 (New Zealand)
Primary Aim	Develop and train a predictive model for relapse risk from RAR data.	Replicate the relapse model in a low-middle income context and test biological correlates of RAR.	Test generalisability of the relapse model to predict treatment response (recovery).
Population	Adults with interepisode BD I or II.	Adults with interepisode BD I or II, plus matched healthy controls.	Adults experiencing an acute manic or depressive episode of BD I or II.
Setting	Outpatients/Community recruitment.	Outpatients/recruitment via hospital-based clinicians.	Predominantly inpatients, some outpatient recruitment via clinicians.
Primary Predictor	Actigraphy (RAR variables) over 14 days (at baseline of three epochs).	Actigraphy (RAR variables) over 14 days (at baseline of one epoch).	Actigraphy (RAR variables) over 14 days (at baseline).
Primary Outcome	Time to Relapse over three 26-week epochs (measured via retrospective LIFE interview on two occasions per epoch).	Time to Relapse over a 26-week epoch (measured via retrospective LIFE interview on two occasions over 26 weeks).	Treatment Response (≥50% symptom reduction) at 8 weeks.
Biological Sampling	No	Yes (blood samples) for circadian gene expression and metabolomics.	No
Clinical Predictors in models	Yes (five key clinical variables included as covariates, e.g., BD subtype, residual symptoms).	Yes (five clinical variables included to enable direct replication of Study 1).	No (to minimise participant burden in an acutely ill population).

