3]. Meeting episode criteria at one of the follow-up interviews is, however, not an exclusion criterion. Considering patient empowerment, risk management and the scientific aims of tracking BD course over an extended period, it was decided on balance to make case-by-case decisions on whether ongoing participation is affected by identification of an episode at a follow-up interview (see below) [
4].

On duty of care grounds, clinical participants in the outpatient Studies 1 and 2 must be currently receiving treatment for BD from a medical practitioner and provide contact details and consent for the doctor to be contacted if required. An additional exclusion criterion in Study 1 and 2 is the presence of active suicidality, measured at baseline and at each follow-up interview. Because of blood draws, a further exclusion criterion in Study 2 only is severe anaemia (Hb level < 7 g/d).

*Study 3*

Study 3 is distinct from Studies 1 and 2 in population, setting and primary outcome (
Box 1). Being in a severe episode of mania or bipolar depression is an inclusion criterion, as defined by a Clinical Global Impression Scale [CGI,
76] of 5 and above, and the majority of participants will be recruited as inpatients. Current intoxication or withdrawal from illicit substances are exclusions unique to Study 3: it is not uncommon for individuals to be admitted to hospital in a state of intoxication or acute withdrawal (e.g., from alcohol or methamphetamines). These states would profoundly impact the capacity to consent and confound the actigraphy data collected in the initial days.

*Written and Informed Consent*

In all studies, written informed consent will be obtained from each participant after they receive detailed explanations about the study procedure in the language best understood by them. Participants can withdraw from the study at any time but will not be able to withdraw data already provided. Participants will be invited to provide ‘extended’ consent so that data can be shared with appropriate research teams upon completion of this project. All participants will be assigned a study ID to be used in place of the participant’s name on all assessment materials. The list linking IDs and names will be held under the same security conditions as study data (see below).

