**Figure 3. f3:**
[figure not shown]
Study 3 design overview.

Study 3 has two additional aims related to improved characterisation of associations between RAR signals and short-term mood dynamics. The secondary aim of Study 3 is to examine the effect of baseline episode polarity—that is, whether the acute episode is depressive or manic—on the performance and structure of the predictive model. The analysis of Study 3’s secondary aim will investigate whether polarity moderates model accuracy against the binary outcome of 50% reduction in symptoms at 8 weeks, using 14 days’ actigraphy data. To increase the granularity of the investigation of this state transition, a tertiary aim of Study 3 is to explore temporal patterns in weekly RAR in relation to weekly clinician ratings of mood (MADRS, YMRS) and clinical state (CGI). The process-focus of this exploratory analysis takes advantage of the full 21 days of actigraphy.

Study 3 therefore investigates the prediction of acute treatment response from RAR variables amongst people who are experiencing a severe episode of BD [an important clinical question in its own right,
78]. Participants will be individuals with BD receiving guideline-based care and treatment
^
75
^ for acute manic (
*N* = 15) or bipolar depressive (
*N* = 30) episodes (on an inpatient, outpatient, or hybrid basis). Participants will be patients of Te Whatu Ora-Waitaha Canterbury Mental Health Services.

Three research questions address the development and testing of a state transition model, and its potential moderation by baseline episode polarity.
•Research Question 1: How many additional samples (
*x*) from the
*N* = 45 Study 3 sample are required to retrain the Study 1 complex system model predicting relapse (
*N* = 75) to achieve acceptable prediction accuracy for
*a state transition model* predicting both relapse amongst interepisode patients and response to treatment amongst acutely ill patients?•Research Question 2: Can a complex system model of state transition trained on
*N* = 75 Study 1 samples and
*x* (from Research Question 1) Study 3 samples predict state transition in an unseen data set of
*N* = 25 Study 1 samples and N = (45 –
*x*) samples from Study 3?•Research Question 3: Is episode polarity at baseline in the Study 3 cohort (
*n* = 30 depression versus
*n* = 15 manic) a moderator for the models developed in Research Question 1 and Research Question 2?

*Work Package 4: Integrative Data Synthesis*

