The extracted indicators will include statistical, time–frequency, and nonlinear features derived from the activity time series and computed over sliding temporal windows, yielding time-varying feature trajectories that reflect changes in system stability. Statistical features (e.g., mean, variance, skewness) will describe overall activity levels; time–frequency features (e.g., spectral power, rhythm amplitude, phase stability) will capture periodicity and circadian patterns; and nonlinear features (e.g., sample entropy, fractal dimension, Lyapunov exponent, correlation dimension, detrended fluctuation analysis) will quantify the complexity and predictability of rest–activity dynamics.

The predictive framework will be implemented using nonlinear dynamic modelling approaches, such as recurrent neural networks (RNNs) or nonlinear autoregressive models, which model sequences of time-indexed feature vectors and are, therefore, well-suited to capturing feedback relationships and temporal dependencies in evolving system dynamics. These models do not explicitly recover the underlying dynamical equations but are designed to learn temporal dependencies in the observed data. These data-driven models are conceptually aligned with Hadaeghi’s formulation of BD as an interacting dynamical system.

The model will be trained to identify patterns and trajectories in these features that precede critical transitions in system stability. In Studies 1 and 2, these transitions will correspond to relapse events among interepisode participants, while in Study 3 they will represent treatment response during acute manic or depressive episodes.

*Input and outcome variables for modelling*

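### Study 3's 14-day recording may include a move between ward and home; if such moves track improvement, the planned features cannot tell a change of setting from system instability

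*Protocol article*

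**What the plan says.** Box 1 gives the Study 3 setting as "Predominantly inpatients, some outpatient recruitment via clinicians". Section 2.1 says that "the majority of participants will be recruited as inpatients", and Section 2.2 allows care "on an inpatient, outpatient, or hybrid basis".

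Participants wear the device for 21 days, but for consistency with Studies 1 and 2 "the first 14 days only will be used in modelling of binary response to treatment" (Section 2.2, Study 3). The outcome runs from the same baseline: "Response to treatment at 8 weeks is operationalised as 50% reduction in MADRS", or the same reduction in YMRS for those who start in mania.

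In the complex system model (Section 2.6), statistical, time-frequency and nonlinear features are "computed over sliding temporal windows, yielding time-varying feature trajectories that reflect changes in system stability". Research Question 1 of Study 3 retrains the Study 1 model with x of the 45 Study 3 participants. Box 1 excludes clinical predictors from the Study 3 models because of participant burden. Section 2.2 adds that, if generalisation is shown, one could hypothesise that the model captures generic system instability and not a process specific to relapse.

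**The concern.** The predictor window lies inside the period in which patients are being treated and may be improving. For a patient who starts on a ward, it may also contain leave or discharge. A move from ward routine to home can shift the level, amplitude and timing of activity abruptly. Features that describe change between windows, such as shifts in variance, rhythm amplitude or phase stability, would register that step.

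If patients who move within 14 days are more often those who respond, the step carries information about the outcome even when the patient's underlying rhythm is no more or less stable than anyone else's. Because the model is retrained on Study 3 patients, it can learn this signal. Nothing in the Study 3 models as described would absorb it.

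What is at stake is mainly the mechanistic reading. Study 3's stated contribution is to show whether one account of instability covers both relapse and recovery. An accuracy that rests on change of setting would not bear on that question.

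**Working it through.** The protocol gives no accuracy target, power figure or length of stay for Study 3, so there is no stated figure to reproduce. The check asks how large the effect could be, and when it disappears.

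**Inputs from the protocol:** a 14-day window from baseline, binary response at 8 weeks, 45 patients, sliding-window features, retraining on x Study 3 patients, and no clinical predictors.

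**Assumed inputs:** overall response 50%; share of recordings with a discharge d = 0.3 or 0.5; odds ratio (OR) between discharge and response of 2, 4 or 6.

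**Step 1: AUC of the marker alone.** Let a = P(discharge | response) and b = P(discharge | no response). Then:

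- a + b = 2d, because response is 50%
- OR = a(1 − b) / [b(1 − a)]
- AUC = 0.5 + (a − b)/2

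For d = 0.5, b = 1 − a, so a = √OR/(1 + √OR) and the AUC equals a. For d = 0.3, substituting b = 0.6 − a gives (OR − 1)a² − (1.6·OR + 0.4)a + 0.6·OR = 0. With OR = 4 this is 3a² − 6.8a + 2.4 = 0, so a = 0.437, b = 0.163 and AUC = 0.5 + 0.274/2 = 0.64.

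| d | OR 2 | OR 4 | OR 6 |
|---|---|---|---|
| 0.3 | 0.57 | 0.64 | 0.67 |
| 0.5 | 0.59 | 0.67 | 0.71 |

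With a = b, that is, discharge unrelated to response, the AUC is 0.50 at any prevalence.

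**Step 2: do window features see the step?** The marker in Step 1 is observed perfectly; the features are not. A simulation used 14 days of hourly activity for 3,000 people per scenario, with 50% response and the same underlying rhythm stability in everyone. Discharge on days 4-12 raised rhythm amplitude from 0.6 to 0.8, 0.9 or 1.1 and shifted phase by 0, 1 or 2 hours respectively. The features were the variability, across 3-day windows, of the standard deviation and of Relative Amplitude.

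| Discharged: responders v non-responders | AUC, marker alone | AUC, window features |
|---|---|---|
| 20% v 20% | 0.50 | 0.49-0.51 |
| 30% v 10% | 0.60 | 0.53-0.61 |
| 50% v 20% | 0.65 | 0.57-0.65 |
| 70% v 20% | 0.75 | 0.61-0.75 |

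A move tied to response is therefore enough to make change-sensitive features appear predictive; a move unrelated to response is not. Not every feature shifts towards apparent instability. In the same runs 14-day Interdaily Stability was higher, not lower, in responders, because amplitude rose after discharge. A retrained model could use either direction.

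**Step 3: precision.** With all 45 patients split 22 and 23, an AUC of 0.64 has a Hanley-McNeil standard error of about 0.083, so the 95% interval is 0.64 ± 1.96 × 0.083, or about 0.48-0.80. The Study 3 part of the test set has only 45 − x patients.

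**The case against.** The two links that drive the size are not in the protocol. It does not say how many patients leave the ward by day 14 or that discharge follows improvement, and hybrid care describes how care is delivered, not a move during the recording. The 14-day sentence chooses 14 days over 21; it is not a rule about setting. Study-level detail is deferred to forthcoming protocols, which may record setting, and Section 2.6 allows clinical data to support interpretation of features. The instability claim is itself tentative, in a project that calls itself exploratory. All of this stands, and it limits the point to what could happen under stated assumptions. It does not remove the point: the window, the features, the retraining, the exclusion of clinical predictors and the intended reading are fixed in this article, and together they do not separate setting from instability.

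A reader might go further and infer that a successful Study 3 model would merely have detected an administrative event. The documents do not support that. If discharge follows improvement, it may genuinely forecast 8-week response, and the damage is to the mechanism and not necessarily to prediction. A reader might also infer that Study 1 recordings contain no comparable step. That is not established: participants who meet episode criteria at follow-up may continue into later epochs, and hospital admissions are among the events to be recorded. Nor can it be said that an AUC of 0.57-0.71 would pass as success. The article sets no threshold, and the prior study it describes reports 0.64 for clinical predictors alone and 0.82 with actigraphy added, for relapse.

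Section 2.6 also treats exogenous influences as part of the model. There, however, they push the system towards instability; a discharge that results from improvement runs the other way.

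**Conclusion.** The point holds in conditional form. If some Study 3 patients change setting within the 14 days, and if that is related to improvement, the planned features can register the move, and successful prediction could not be taken as support for generic system instability. Under 30-50% of recordings with a discharge and odds ratios of 2-6, the marker alone gives an AUC of about 0.57-0.71. Window features capture part or all of such a signal, depending on the assumed size of the shift. If discharge is unrelated to response, the effect vanishes. The documents do not show which case applies. They do not support calling the design invalid or replacing its primary model.

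**What to change.** Keep the 14-day primary model, and add the following:

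1. **Record setting for each actigraphy day**, from the dates of admission, overnight leave and discharge. Section 2.9 says data collection has commenced, so dates for those already enrolled would come from the hospital record.
2. **Report two comparators**: the AUC of change of setting by day 14 (yes/no), and the AUC of early symptom change from the weekly MADRS and YMRS ratings already collected. Report whether the rest-activity features add to them. This needs no new assessments, so the burden argument in Box 1 is respected.
3. **Add a sensitivity analysis in which recording length does not depend on discharge**: either patients with no change of setting in the 14 days, or one short initial window of the same length for everyone. Cutting each recording at discharge is not a sound alternative. On the premise of this concern, recording length would then depend on improvement, and a sequence model or a length-sensitive nonlinear feature could read early discharge from the length alone.
4. **Limit the instability interpretation** to a signal that persists in these analyses.

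The cost is a few dates per patient and extra analysis runs. Restricting to unmoved patients selects a subgroup, and a short common window discards data. With 45 patients or fewer the comparisons will be imprecise, so they should be reported as estimates with intervals and not as pass-or-fail tests.
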